### Recruitment

All patients (>18 years of age) referred to the endoscopy department for routine diagnostic upper GI endoscopy and diagnosed with CAG or IM between November 2018 and June 2020 are eligible for inclusion if able to give informed consent. Patients are excluded when having (1) gastric neoplasia not amenable to endoscopic resection, (2) no indication for Sydney biopsy staging on standard WLE, (3) significant comorbidity, (4) a coagulation disorder, (5) previous gastric surgery or (6) are unable to complete the biopsy protocol in either endoscopy session.

## Interventions

### Baseline characteristics

All patients are asked to complete a questionnaire on lifestyle factors, medical history, past interventions, medication use and family history of gastric cancer.

### White light endoscopy

Patients referred to the endoscopy department for upper GI endoscopy for investigation of symptoms or for surveillance of a known condition will undergo their procedure on a standard diagnostic gastroscopy list. Patients found to have CAG or IM will be prospectively identified. During the initial procedure, patients will receive the current recommended practice. Current practice is to initially identify if gastric atrophy is present and to inspect the gastric mucosa for areas suspicious for dysplasia or malignancy. Any mucosal abnormalities suspicious for dysplasia or malignancy are biopsied with tissue biopsies placed in separate containers. Following this, 10 random biopsies are taken according to the Sydney protocol (see also figure 2): 4 quadrant biopsies of the antrum, 2 biopsies from the incisura and 4 biopsies from the body of the stomach, respectively, 2 from the lesser curve, and 2 from the greater curve.

### Enhanced imaging endoscopy

**Figure 2 F2:**
[figure not shown]
Biopsy strategy. (A) Sydney protocol biopsy sites in the opened stomach along the greater curvature; (B) biopsy sites in the anatomical view.

Patients who opt to be recruited to the study will be invited for a second endoscopy at 6–12 months interval. This will be performed by one of the experts on this protocol. The endoscopists will be blinded to any previous endoscopy or biopsy results. This second endoscopy will be recorded and performed using enhanced endoscopic imaging. Given that these patients will have recently undergone a complete upper GI endoscopy, while all anatomical landmarks will be viewed, the focus of this examination will be on the gastric mucosa. The endoscopist will record (1) the extent of gastric atrophy, (2) the presence and extent of IM in each of the aforementioned areas. This will be done using our simplified endoscopic metaplasia scoring system (GRAHAM Score) (table 1).

**Table 1 T1:** Simplified endoscopic gastric intestinal metaplasia staging system: ‘GRAHAM Score’

	Focal/minimal metaplasia (<1/3 of surface coverage)	Moderate/extensive metaplasia (>1/3 surface coverage)
Antrum and incisura	1	2
Lesser curve	1	2
Greater curve	1	2

Biopsies will then be taken in the following manner: (1) areas of IM found in any of the Sydney protocol areas, (2) Sydney areas negative for GIM will be randomly biopsied, as control, to complete the assessment and (3) lesions suspicious for dysplasia or malignancy.

### Histopathological assessment

Each biopsy will be reviewed at the teaching hospital by one of the expert GI histopathologists named on this protocol according to the established operative link for gastritis assessment and operative link for gastric intestinal metaplasia assessment staging systems.^21^ Histopathologists will be blinded to whether biopsies were directed at areas suspicious for IM and to the biopsy results of WLE staging. A proportion of biopsy samples will be reviewed and rescored by a second expert GI histopathologist, who is blinded to the initial results. This is to ensure interobserver reproducibility for histopathological detection of IM.

### Serology assessment

A proportion of the collected serum will be used to assess *Helicobacter pylori* serology, pepsinogen I/II ratio and gastrin-17. The remaining serum will then be stored for use in future studies exploring the development of molecular biomarkers for gastric atrophy risk stratification.

### Data collection and management

All data collected for this study will be recorded in an anonymised format on a centralised, secure web-based platform (OpenClinica). Source data will be recorded in patients’ notes or electronic health records, and hard copies of consent forms will be stored in a secure locked cabinet per site. All study data will be stored in a linked anonymised fashion against a study number, with the registry of study numbers stored separately on an encrypted database.

### Statistical analyses

For descriptive statistics, mean (±SD) will be used in case of a normal distribution of variables and median (25–75%) will be used for variables with a skewed distribution. Where appropriate, the Student’s t-test or Mann–Whitney U test will be used.

Diagnostic accuracy of endoscopic diagnosis of CAG and IM is defined as the total number of directed biopsies that confirm the endoscopic impression of the presence or absence of IM divided by the total number of biopsies (accuracy=true positives+true negatives/all biopsies). Results will be compared with the histopathology outcomes using the χ^2^ test after multiple testing correction as well as kappa values for interobserver agreement among endoscopists and histopathologists.

After study completion, all videos will be collated and anonymised prior to expert panel review and estimation of the severity and extent of atrophy as well as IM. Five expert reviewers will review 50 videos each (kappa 0.4) for the purposes of assessing interobserver reliability. Sensitivity, specificity and global accuracy along with the 95% confidence intervals will be established. Duration of inspection time of gastric mucosa and its relation to diagnostic accuracy will be evaluated using, when appropriate, a paired t-test or Wilcoxon test. All tests will be two-sided.

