### Design

This is a prospective, multicentre registry study on the accuracy and reproducibility of enhanced endoscopic imaging, including high-definition WLE and virtual chromoendoscopy, for the staging of CAG and IM. Two upper endoscopies will be performed on two separate occasions (6–12 months in between) using standard white-light endoscopy plus random biopsies (current diagnostic strategy) at the first endoscopy and enhanced endoscopic imaging with targeted biopsies (proposed diagnostic strategy) at the second endoscopy. We will compare both approaches using histopathology as a reference and assess the accuracy and reproducibility of enhanced endoscopic imaging (figure 1).

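### The χ² test on individual biopsies ignores clustering within patients and tests association with histology, not the within-patient difference between the two strategies

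*Protocol article*

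**What the plan says.** All places are in the protocol article.

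- **Statistical analyses** makes the biopsy the unit of accuracy. The numerator is "the total number of directed biopsies that confirm the endoscopic impression of the presence or absence of IM" and the result is "divided by the total number of biopsies". The next sentence names the test: "Results will be compared with the histopathology outcomes using the χ^2^ test", with a multiplicity correction, and kappa for agreement between observers. Sensitivity, specificity and accuracy are to have 95% confidence intervals, with no method given. The only paired tests named (t-test or Wilcoxon) are for inspection time.
- **White light endoscopy** fixes the first session: "10 random biopsies are taken according to the Sydney protocol".
- **Enhanced imaging endoscopy** gives no count for the second session, but every Sydney area is sampled: areas with visible metaplasia are biopsied, and "Sydney areas negative for GIM will be randomly biopsied, as control, to complete the assessment".
- **Design** has each patient examined twice: "Two upper endoscopies will be performed on two separate occasions". The intent is stated as "We will compare both approaches using histopathology as a reference".
- **Aims** makes the comparison of the two strategies the primary aim, and **Sample size** derives 234 patients from a 10-point difference in sensitivity between them.

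**The concern.** Two separate things are wrong with the named test.

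**Independence.** Biopsies from one stomach share the same disease and, at the second session, one endoscopist and one examination. Correct and incorrect calls will tend to cluster within patients. A Pearson χ² test on pooled biopsies counts each one as a separate unit of information.

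**The question asked.** A χ² test of endoscopic impression against histology has no association as its null hypothesis. Rejecting it shows that endoscopy is better than guessing. It does not show that accuracy is high, or that enhanced imaging does better than white light endoscopy (WLE) with random biopsies. That second question is why each patient has two endoscopies and why 234 are recruited.

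At stake are overstated precision for the accuracy results and a significant primary p-value that does not bear on the primary aim.

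**Working it through.** **Inputs from the article:** 234 patients; 10 biopsies per patient at session 1; biopsy as the unit for accuracy; two-sided alpha 0.05. **Assumed, because not given:** within-patient correlation ρ of 0.1 to 0.3; 5 to 10 biopsies per patient at session 2; 40% prevalence of metaplasia among biopsies.

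**The plan's own figure.** The 234 is used here only as a multiplier. It does not follow directly from the stated inputs. With 90% versus an assumed 80%, 80% power and two-sided alpha 0.05, two independent groups need 199 each (219 with continuity correction). A McNemar calculation with an assumed discordance of 0.30 gives (1.96·√0.30 + 0.842·√0.29)²/0.01 ≈ 233.1, so 234. That is a separate matter, and nothing below depends on it.

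**1. Clustering.** For a proportion over m biopsies per patient, the design effect is DE = 1 + (m − 1)ρ and the effective number of biopsies is 234m/DE. A nominal 95% simple binomial interval then covers 2Φ(1.96/√DE) − 1.

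| m | ρ | DE | Biopsies | Effective number | Coverage |
|---|---|---|---|---|---|
| 10 | 0.1 | 1.9 | 2,340 | 1,232 | 84% |
| 10 | 0.2 | 2.8 | 2,340 | 836 | 76% |
| 10 | 0.3 | 3.7 | 2,340 | 632 | 69% |
| 5 | 0.1 | 1.4 | 1,170 | 836 | 90% |
| 5 | 0.2 | 1.8 | 1,170 | 650 | 86% |
| 5 | 0.3 | 2.2 | 1,170 | 532 | 81% |

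These design effects are for a proportion such as accuracy. For the association test, the distortion depends on how strongly both the endoscopic impression and the histology cluster, so no type I error is quoted for it.

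**2. What the association test detects.** Take sensitivity 55%, specificity 52% and prevalence 40%.

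- Accuracy = 0.40·0.55 + 0.60·0.52 = 0.532.
- Proportion called positive: q = 0.40·0.55 + 0.60·0.48 = 0.508.
- φ² = (0.55 + 0.52 − 1)²·0.40·0.60 / (0.508·0.492) = 0.0047.
- Non-centrality is nφ² = 11.0 for n = 2,340 and 5.5 for n = 1,170.
- Power at alpha 0.05 is Φ(√11.0 − 1.96) = 91% and Φ(√5.5 − 1.96) = 65%.
- At alpha 0.01 (an illustrative five-fold Bonferroni correction) with n = 2,340, power is Φ(√11.0 − 2.576) = 77%.

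These powers treat biopsies as independent, as the named test does.

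**3. If χ² were used between sessions instead.** The article does not say this. With correlation ρw within a session and ρb between sessions, and equal numbers of biopsies, the variance ratio is V = 1 + (m − 1)ρw − mρb and the real type I error is 2(1 − Φ(1.96/√V)). For m = 10 and ρw = 0.1/0.2/0.3:

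- ρb = 0: V = 1.9/2.8/3.7, error 16%/24%/31%.
- ρb = ρw/2: V = 1.4/1.8/2.2, error 10%/14%/19%.
- ρb = ρw: V = 0.9/0.8/0.7, error 4%/3%/2%.

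A simulation (234 patients, 10 biopsies per session, 85% accuracy at both, 2,000 runs) agreed. The naive test rejected in 16% to 24% of runs when biopsies of the same session were correlated, and in 3% when only a stable patient effect was present. A patient-level paired test rejected in 4.6% to 4.9% in all these settings.

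**The case against.** The strongest reply is that a journal article condenses the full protocol, so the absence of a paired test or an interval method is no fault. That stands for omissions. It does not rescue the sentence that is there: the article chooses the biopsy as the unit of accuracy and names the test, and that pairing does not fit the stated aim.

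Other parts of the reply also stand and limit the point:

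- A reader might infer that the planned confidence intervals are wrong. No interval method is given, so the coverage figures apply only if simple binomial intervals on biopsies are used. The biopsy denominator is also stated only for accuracy. Sensitivity is the sample-size quantity, and that is counted in patients.
- A reader might infer 10 biopsies at both sessions. The number is documented only for session 1, and the accuracy definition concerns directed biopsies, which belong to session 2. Hence the range down to 5.
- A reader might infer that the strategy comparison has an inflated type I error. The article assigns no test to that comparison, and if χ² were borrowed for it the error could fall on either side of 5%.
- The planned multiplicity correction lowers the chance that a poor reading reaches significance (77% rather than 91% in the illustration). Accuracy would also be reported beside the p-value, so a value of 53% would be visible.

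**Conclusion.** The point holds in this form. As written, the χ² test on biopsies ignores clustering within patients and tests association with histology, so it cannot establish the within-patient difference between strategies that is the aim and the sample-size basis. The mismatch between test and question needs no assumption about correlation.

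The size of the clustering effect does need one. With ρ of 0.1 to 0.3, pooled biopsies carry the information of about one half to one quarter of their number at 10 per patient (1/1.9 to 1/3.7), and about 70% to 45% at 5 per patient (1/1.4 to 1/2.2).

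The documents do not support saying that every p-value would be too small or that the reported intervals are certain to be too narrow.

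**What to change.** Replace the χ² test as the primary analysis.

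1. Report sensitivity, specificity and accuracy of enhanced imaging with 95% intervals from a cluster-robust variance or a bootstrap that resamples patients.
2. Test the enhanced-minus-WLE contrast as a paired difference with its 95% interval, on an outcome available at both sessions. An example is metaplasia detected per Sydney location or per patient, against one stated common reference. Use McNemar at patient level, or a GEE or mixed logistic model clustered on patient, with session as factor and location as covariate.

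Two things must be settled first. The article describes recording of metaplasia by area only at the second endoscopy, so correctness of the endoscopic call can be the paired outcome only if such a call is also recorded per location at WLE. The Sample size section makes WLE with random biopsies the reference while Design makes it one of the two strategies compared against histopathology, so the common reference has to be stated.

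The cost is revised analysis wording, slightly more analysis work and wider single-session intervals. No extra patients or procedures are needed for this change.

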## Methods and analysis

### Aims

The primary aim of this study is to assess the diagnostic accuracy for the endoscopic diagnosis of IM in Sydney biopsy locations comparing standard endoscopic staging with random biopsies with enhanced imaging with biopsies targeted to GIM.^19^ The Standards for Reporting of Diagnostic Accuracy Studies (STARD) guidelines were followed.^20^ Study sites are located in the Netherlands and the UK. Secondary objectives are to evaluate (a) reproducibility of endoscopic staging after expert review, (b) reproducibility of histopathology for detection of IM, (c) the number of dysplastic or neoplastic lesions detected and (d) effects of inspection time of gastric mucosa on diagnostic accuracy.

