Over the years, serological markers have shown major promise for predicting the presence and severity of gastric premalignant lesions.^25–27^ Pepsinogens are serological markers for atrophy in the stomach and can be divided into pepsinogen I and II. A decreased PG I/II ratio indicates the presence of atrophic changes. Gastrin serum levels are indicative for gastric acid output and are increased in the presence of atrophic changes.^27^ The collection of serum samples was included in our protocol to strengthen risk stratification for progression of premalignant gastric lesions.

A few limitations of the study should be mentioned. All high-definition endoscopies will be performed by expert endoscopists at either site. A potential caveat with this design is the generalisability of the study outcomes to non-expert settings. To test this, we selected a panel of independent endoscopists who will review recorded endoscopy videos in order to assess interobserver variability. The same limitation holds for the histopathological evaluation of the biopsy samples. Therefore, a proportion of the samples will be reviewed and rescored by a blinded second expert GI histopathologist.

In conclusion, prospective validation of endoscopy-led staging of the premalignant stomach will provide the needed evidence for an endoscopy-led risk stratification of patients at risk for gastric adenocarcinoma. This will allow rational design of tiered screening and surveillance protocols to benefit early stage gastric cancer detection within at-risk populations. This will cause major implications for affected patients and general healthcare resource utilisation.

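### Anonymising the panel videos does not hide where the index expert aimed the biopsies, which leaves an avoidable upward bias in the agreement estimate for secondary objective (a)

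*Protocol article*

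**What the plan says.** Four parts of the protocol article bear on this.

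- **Enhanced imaging endoscopy, recording:** "This second endoscopy will be recorded and performed using enhanced endoscopic imaging". The expert scores the extent of atrophy and of IM during the examination.
- **Enhanced imaging endoscopy, biopsies:** sampling follows the scoring in the same session. "Biopsies will then be taken in the following manner: (1) areas of IM found in any of the Sydney protocol areas"; next, "Sydney areas negative for GIM will be randomly biopsied, as control, to complete the assessment"; and finally any lesion suspicious for dysplasia or malignancy.
- **Statistical analyses:** after the study ends, "all videos will be collated and anonymised prior to expert panel review". The panel's task is "estimation of the severity and extent of atrophy as well as IM", and "Five expert reviewers will review 50 videos each (kappa 0.4) for the purposes of assessing interobserver reliability".
- **Aims and Discussion:** the objective served is "reproducibility of endoscopic staging after expert review", secondary objective (a). The Discussion answers the concern that only experts perform the procedures by saying that "we selected a panel of independent endoscopists who will review recorded endoscopy videos in order to assess interobserver variability".

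The article does not say that the biopsy phase is removed from the panel videos, or that the panel is masked to the index endoscopist's findings. Nor does it say that reviewers see the recordings uncut.

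**The concern.** An agreement study needs each rater to judge the mucosa without knowing what another rater concluded. Here the index expert's conclusion is partly acted out on screen, because forceps go deliberately to the patches judged to be IM. Anonymisation removes identity and leaves that in place.

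The article already treats this kind of information as able to bias a reader. Under Histopathological assessment, the pathologists are kept unaware of whether a biopsy was aimed at suspected IM, and the second pathologist is masked to the first reading. The second endoscopist is masked to the first endoscopy. The panel is the one group that could watch the targeting directly, and for it the article offers only anonymisation and the word independent.

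At stake is the credibility of the reproducibility result. The panel is also the article's stated answer to its main limitation on generalisability. A kappa that is partly the product of a shared cue would make that answer look stronger than it is.

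**Working it through.** **1. Is there a cue, and how much does it reveal?** Put the biopsy rules side by side. IM areas receive targeted biopsies; Sydney areas without IM receive random ones. Every Sydney area is therefore sampled whatever the call, and the presence of forceps in an area tells the reviewer nothing by itself. What remains is how the biopsy is placed (aimed at a visible patch or placed at random) and possibly the order of sampling. Spoken commentary would add to this if sound is recorded, which the article does not mention. The cue concerns IM; no biopsy is described as aimed at atrophy.

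**2. The plan's own figure.** The article gives 50 videos per reviewer and a kappa of 0.4, with no precision, null value or power. That figure cannot be re-derived, and this point does not depend on it. It serves only to place the illustration below at a similar baseline.

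**3. Illustration of size.** All inputs here are assumptions; none is in the article.

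- Yes/no IM call per site, with half of sites truly positive.
- Sensitivity and specificity of 0.82 for every reader and for the index expert, with errors independent given the truth.
- A share q of each reviewer's calls simply repeats the index expert's call.

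*Baseline.* Two independent readers agree with probability 0.82² + 0.18² = 0.6724 + 0.0324 = 0.7048. Chance agreement is 0.5. Kappa = (0.7048 − 0.5) / 0.5 = 0.41 (0.4096).

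*Reviewer against index expert.* A copied call agrees for certain and an uncopied call has the baseline kappa. The margins stay at one half, so kappa = q + (1 − q) × 0.4096.

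*Reviewer against reviewer.* Agreement is certain only when both copy (probability q²). In all other cases the baseline holds, so kappa = 0.4096 + 0.5904 × q².

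| q | Against index expert | Among reviewers |
|---|---|---|
| 0 | 0.41 | 0.41 |
| 10% | 0.10 + 0.90 × 0.4096 = 0.47 | 0.4096 + 0.0059 = 0.42 |
| 20% | 0.20 + 0.80 × 0.4096 = 0.53 | 0.4096 + 0.0236 = 0.43 |
| 30% | 0.30 + 0.70 × 0.4096 = 0.59 | 0.4096 + 0.0531 = 0.46 |

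Both formulas increase with q, so in this model the bias runs in one direction. A simulation with a baseline of 0.40 and q up to 50% shows the same pattern: at q = 50%, 0.55 among reviewers and 0.70 against the index expert.

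**4. Compared with sampling error.** Simulating five readers with 50 yes/no ratings each under the assumptions in step 3, the kappa among reviewers has a standard deviation of about 0.07. The shift at q = 30% (0.46 − 0.41 = 0.05) is smaller than that; the shift at 10% is negligible. The shift against the index expert at q = 30% is 0.59 − 0.41 = 0.18.

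**The case against.** **This is only silence in a condensed article.** Preparing clips and masking readers are operational details that a full protocol may cover. This stands in part: a reader might infer that the panel watches the entire uncut procedure, and the article does not say so. But it does describe how the videos are prepared, and the one safeguard it names does not address this leak. It also spells out masking for the other key readers.

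**Negative areas are biopsied too.** This stands. A reader might infer that forceps on screen mark a positive call; the random control biopsies rule that out. The cue is weakened to aim and order, but not removed.

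**The model is not the outcome rated.** This also stands. The panel grades severity and extent, of atrophy as well as IM, and the article's IM score turns on whether more or less than one third of the surface is covered. A biopsy site does not directly disclose coverage, and the atrophy ratings have no stated targeting cue. The yes/no model with outright copying shows direction and possible size only.

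**The larger figures may not apply.** The article ties the panel to interobserver reliability without saying whether the index expert counts as one of the compared raters. If not, only the smaller shift, 0.41 to at most 0.46 for q up to 30%, is relevant.

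**Conclusion.** The point holds as an avoidable risk of bias. Followed as written, the plan lets reviewers see where the index expert targeted IM, and any use they make of that raises measured agreement. If 10% to 30% of calls followed the cue, a kappa of about 0.41 would read 0.42 to 0.46 among reviewers and 0.47 to 0.59 against the index expert. These figures rest on the assumed copying share, accuracy, prevalence and yes/no scale.

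Two stronger readings are not supported. The article does not show that kappa will be inflated: that depends on what the clips contain and how far reviewers use the cue, neither of which it states. Nor does the point touch the primary result, which compares the index endoscopist's own impression with histology and does not use the panel. Only secondary objective (a) is affected. The change is worth making because it is cheap and removes a bias that favours the hoped-for conclusion.

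**What to change.** Show the panel only the inspection phase: end each clip before the first biopsy and remove any audio. State in the protocol that reviewers are masked to the index endoscopist's scores and biopsy sites. Because scoring comes before biopsy, the cut is intended to keep the inspection on which the index score was based. The full recordings can be kept in the archive. If the full protocol already trims the videos this way, one sentence saying so settles the point.

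The cost is a few minutes of editing per reviewed video: 50 videos if all five reviewers see the same set, or up to 5 × 50 = 250 if their sets differ, which the article leaves open. Review takes place after study completion, so nothing in the conduct of the endoscopies changes.

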## Participants

### Sample size

For estimation of sample size, we assume that the diagnosis of CAG or IM on enhanced imaging and targeted biopsies must be set with at least a 90% sensitivity with WLE and random biopsies as a reference.^15^ A power (beta) of 80% and a probability of type I error (alpha) of 0.05 will be handled. That purpose requires at least 234 patients to be recruited to show a 10 % difference in sensitivity between enhanced endoscopy-led staging and the standard WLE.

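### The paired test named for inspection time does not validly answer secondary objective (d), the relation of inspection time to diagnostic accuracy

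*Protocol article*

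**What the plan says.** The Aims section of the protocol article lists, as secondary objective (d), "effects of inspection time of gastric mucosa on diagnostic accuracy". This is a question about an exposure and an outcome: does accuracy change with time spent looking?

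The Statistical analyses section assigns the method: "Duration of inspection time of gastric mucosa and its relation to diagnostic accuracy will be evaluated using, when appropriate, a paired t-test or Wilcoxon test". The same section defines the outcome as a proportion of biopsies, "accuracy=true positives+true negatives/all biopsies", and adds "All tests will be two-sided". For unpaired comparisons it names other tests in its descriptive paragraph: "t-test or Mann–Whitney U test will be used".

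The only pairing that the design itself supplies is the patient's two examinations: "Two upper endoscopies will be performed on two separate occasions", with white light first and enhanced imaging second. For this objective the article names no regression, no correlation and no comparison of accuracy across groups of inspection time.

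**The concern.** A paired t-test or signed-rank test looks at within-pair differences in a single variable. Inspection time is in minutes and accuracy is a proportion, so the two cannot be differenced against each other. The likely pair is therefore time with time, which shows only whether one examination took longer than the other.

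What is at stake is the answer to objective (d). The planned p-value could be reported under that objective although it concerns a different question. A longer enhanced examination, together with better accuracy at that examination, could then be taken as evidence that longer inspection improves accuracy. A real relation within the enhanced session could also go unexamined. The primary accuracy comparison is not touched.

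**Working it through.** The article gives no sample size, effect size or power for objective (d), so there is no stated figure to reproduce. The check is of what each possible pairing estimates, followed by an illustration.

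**Step 1: possible pairings.**

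- *Time at endoscopy 1 against time at endoscopy 2.* For patient i, d_i = t_1i − t_2i, and the paired t statistic is mean(d) / (s_d/√n). The signed-rank test uses the ranks of |d_i| and the signs. Accuracy appears in neither.
- *Patients correct at one session and wrong at the other, comparing the two times.* Accuracy now decides who is included and the direction of the difference. But the order is fixed by the Design section, the imaging method differs by session, and the second examination is done by a study expert while the first takes place on a routine list. A time difference cannot be separated from these.
- *Correct against incorrect biopsies within one examination.* If time is one value per examination (an assumption; the article does not say), every paired difference is zero.

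None of the three gives an interpretable relation of time to accuracy.

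**Step 2: which Wilcoxon test.** The unpaired rank test is named separately in the same section as Mann–Whitney U. Wilcoxon stands directly beside the paired t-test. Signed-rank is the natural meaning.

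**Step 3: illustration of the first pairing.** From the article: n = 234 ("requires at least 234 patients to be recruited", set for the primary comparison and used here only as n), two-sided tests and alpha 0.05. Assumed, not in the article:

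- inspection time with mean 8 min and SD 2 at each endoscopy, drawn independently;
- 10 biopsies per patient;
- accuracy 85% at the mean time;
- log-odds slope of 0 or 0.2 per minute;
- difference in mean time between sessions of 0 or 2 min.

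A slope of 0.2 is an odds ratio of exp(0.2) = 1.22 per minute. The odds at the mean are 0.85/0.15 = 5.667. Two minutes less gives 5.667 × exp(−0.4) = 3.80, or 79% accuracy; two minutes more gives 5.667 × exp(0.4) = 8.45, or 89%.

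Rejection rates over 1,500 runs, with a Spearman test of time against per-patient accuracy as the direct comparator:

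| Slope per min | Mean time difference | Paired t | Signed-rank | Spearman |
|---|---|---|---|---|
| 0 | 0 min | 4.7% | 4.8% | 4.9% |
| 0.2 | 0 min | 5.8% | 5.8% | 100% |
| 0 | 2 min | 100% | 100% | 4.3% |
| 0.2 | 2 min | 100% | 100% | 100% |

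The simulation error at a true rate of 5% is √(0.05 × 0.95/1,500) = 0.6 percentage points, so 5.8% is compatible with alpha. The paired tests follow the difference in mean time and do not respond to the slope. The percentages depend on the assumed inputs; the pattern follows from Step 1.

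**Step 4: the unpaired reading.** If a rank-sum test of time in correct against incorrect diagnoses were meant, with one binary result per patient, it would reject in 5.1%, 55.2% and 89% of runs at slopes 0, 0.2 and 0.3. That is a test of association, but it gives no estimate of how accuracy changes per minute.

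**The case against.** The strongest reply is that the article does not define the pair, does not write signed-rank, and lets the test be chosen as appropriate. A comparison of time between correct and incorrect diagnoses would be a crude test of the relation, and Step 4 shows that it responds to it. A further reply is that the article is condensed, and the model for the last of four secondary objectives could be left to an analysis plan.

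Part of this stands. A reader might infer that the planned test carries no information on accuracy under any reading, or that its p-value can never depend on the accuracy data. The article does not support that: it holds for the between-session pairing only. The simulation shows what that pairing implies, not which pairing was intended. The article also does not say that inspection time is recorded at the first endoscopy; only the second is said to be recorded.

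A reader might also multiply 234 by ten biopsies and expect 2,340 separate endoscopic calls for the analysis. The count of ten belongs to the white light session; no count is given for the enhanced session. Several biopsies may share one endoscopic call, and 234 is a recruitment minimum, not a number of completed second endoscopies.

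The rest does not rescue the plan. A rank-sum comparison is not what the wording says, and the paired t-test named beside it would still not fit. Pairing on discordant correctness is confounded by design. This is also not a detail left open: the article names a method, and the method does not match the objective.

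**Conclusion.** The point holds in a limited form. The article assigns a paired test to the relation between time and accuracy without saying what is paired. On its most natural reading the test compares durations only, and the paired alternative that uses accuracy confounds time with imaging method, operator and order. Objective (d) is therefore not validly answered by the stated analysis.

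This rests on reading Wilcoxon as signed-rank and on the two endoscopies as the source of pairing. Both are inferences from the wording and design, not explicit statements. The paired tests remain valid for comparing duration between sessions, so the half of the sentence about duration is covered.

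The importance is moderate: one secondary objective is affected, and the sample size and primary comparison are unchanged. It is still worth correcting, because the remedy is small and uses the time and accuracy data that objective (d) already requires.

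**What to change.** State the analysis for objective (d) as follows.

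- Within the enhanced-imaging session, take the endoscopic call as correct or not against histology, per biopsy or per location, and state which.
- Relate it to inspection time in minutes with a logistic GEE or mixed model that accounts for clustering within patient. Allow for endoscopist as far as the number of endoscopists permits; the article does not give that number, and with few of them cluster-robust errors at that level would be unreliable.
- Report the odds ratio per minute with its 95% CI.
- Define how inspection time is measured. Whether time spent on biopsies can be separated out depends on timing data that the article does not describe.
- Keep any adjustment for IM extent as a sensitivity analysis using histological extent. Endoscopically scored extent may itself depend on how long the endoscopist looks.
- Keep the paired test only to describe duration between sessions, if time is recorded at both.

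The cost is a change of wording and one extra model. Time is not randomised, so the result is an observational association and should be labelled exploratory.
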